##### FCR assessments

FCR screening will be completed using two measures below:Fear of Cancer Recurrence Inventory – Short Form (FCRI-SF): The FCRI-SF [35] is a 9-item instrument assessing the presence, frequency, intensity, and duration of thoughts associated with FCR. Total scores range from 0 to 36 with higher scores indicating higher FCR. The FCRI-SF has shown strong internal consistency (*α* = 0.95), temporal stability (*r* = 0.89), and construct validity.Fear of Cancer Recurrence – One Item Measure (FCR-1): The FCR-1 is a one-item measure assessing the severity of FCR [23, 36]. Survivors are asked to rate their fear of their cancer returning or getting worse on a scale from 0 (no fear) to 10 (worst possible fear). In its initial validation study, the FCR-1 was responsive to changes in FCR over time and showed concurrent, convergent, and discriminant validity [36]. This measure is included to provide further validation and comparison against the FCRI-SF.

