#### Study procedures

Over a 15-week period, eligible survivors who have completed screening will be invited to participate in the *Fear-Less* program. Survivors who provide consent to participate will be stratified into a specific level of care within the stepped-care program based on their screening score on the FCRI-SF [35, 38, 39].

Participants identified as experiencing low FCR (score of <13 on the FCRI-SF) will continue with their usual care with their medical and nursing teams. No further follow-up or additional screening will be undertaken for these participants.

Participants identified as experiencing moderate/subthreshold levels of FCR (score of 13–21 on FCRI-SF) will have a brief discussion with a psychologist on the research team to confirm they are concerned about their level of FCR and would like support for it. Participants who agree to proceed will be offered the clinician-guided self-management intervention.

Participants identified as experiencing high/clinical levels of FCR (score of ≥22 on the FCRI-SF) will have a brief discussion with a psychologist on the research team member to confirm the severity of FCR and whether they would like support for it. Factors that will be assessed during this discussion will include the frequency, emotional impact, functional impact, and avoidance of FCR. Participants whose assessment indicates clinical levels of FCR will be offered ConquerFear. Participants who are considered to have sub-threshold FCR, or who do not wish to take part in the ConquerFear therapy, will be offered the self-management intervention.

Following each intervention, participants will complete the screening questionnaires and a survivor experiences survey relevant to the intervention they received. To minimize missing data, questionnaires and surveys not returned within 2 weeks of receipt will be followed-up by phone and mail/email up to three times, at 2-week intervals. Options for follow-up treatment will also be discussed depending on the survivors’ needs. This may include no further treatment, or referrals to services such as a psychiatrist, additional individual therapy, or peer supports.

The three levels of interventions are summarised in Fig. 1.

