##### Impact

Change scores between pre- and post-intervention FCRI-SF will be calculated to describe the impact of the *Fear-Less* interventions. Participants who report a reduction of 10% or more on the FCRI-SF (indicative of a clinically significant improvement [43]) will be considered to have a reduction in FCR.

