## Discussion

Approximately 50% of cancer survivors experience moderate-to-high levels of FCR [2, 3], which left untreated, are associated with poorer health outcomes [5, 7–9]. Support for FCR remains a significant unmet need for cancer survivors, where systemic barriers to identifying and treating FCR include lack of routine screening and limited resources to provide interventions for individuals experiencing FCR [22, 23]. Specific strategies, such as a stepped-care approach and the refinement of interventions included in this approach, may provide a solution to these barriers [26].

The *Fear-Less s*tepped-care model provides a framework for screening FCR and stratifying survivors to the appropriate level of treatment, so that the more intensive ConquerFear is reserved for individuals with clinical FCR. This is a novel model of care that has shown promising outcomes with a stage IV melanoma population [32]. Our study will provide an indication of whether this model is also feasible and acceptable amongst early-stage cancer survivors.

Additionally, our study will contribute to the growing literature regarding less intensive FCR interventions. As described by Pradhan et al. [26], there are currently few minimal interventions for FCR that can be implemented within a stepped-care approach. The outcomes from our evaluation will provide an indication of whether our purpose-developed self-management resource is acceptable and feasible to participants and improves FCR levels.

Should this be the case, further investigations regarding the efficacy and cost-effectiveness of *Fear-Less* can be conducted.

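### The 10% FCRI-SF improvement rule lies inside retest error at the protocol's own reliability for any SD of about 4.4 or more, and a single arm cannot show how many responders arise without true change

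*Protocol article*

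**What the plan says.** The Impact section of the protocol article first says that FCRI-SF change scores from before to after the intervention will describe impact. It then adds a classification. Those counted as having reduced FCR are "Participants who report a reduction of 10% or more on the FCRI-SF", and the article glosses the threshold, by citation, as "indicative of a clinically significant improvement". It does not say whether the 10% is of the participant's own baseline or of the scale.

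Under FCR assessments the scale is described: "Total scores range from 0 to 36 with higher scores indicating higher FCR". Its reliability is given there too: "The FCRI-SF has shown strong internal consistency (*α* = 0.95), temporal stability (*r* = 0.89), and construct validity".

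Under Study procedures the interventions go to two bands, a "score of 13–21 on FCRI-SF" for self-management and a "score of ≥22 on the FCRI-SF" for ConquerFear. Participants below 13 are not measured again. Table 1 shows that the screening score is also the only FCRI-SF score before the intervention. Study design describes a single arm. The Discussion expects the results to indicate whether the booklet "is acceptable and feasible to participants and improves FCR levels", and makes later efficacy and cost-effectiveness work depend on that.

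**The concern.** Ten per cent of a score between 13 and 36 is only a few points. If two measurements of an unchanged person commonly differ by that much, the rule will count retest variation as improvement.

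Three features of the design make this hard to see in the results:

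- There is no comparator, and low scorers are not measured again, so the rate without treatment is not observed.
- Participants are selected on the same score that serves as baseline, so scores will tend to fall on remeasurement (regression to the mean).
- Only reductions are classified, so no worsening rate stands beside the improvement rate.

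At stake is the reading of the one responder percentage in the plan. An inert intervention could show a sizeable share of participants labelled as clinically improved, and that could be taken as support for the booklet.

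**Working it through.** The article states no expected responder rate, so there is no figure of its own to reproduce.

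**Inputs from the article:** range 0–36, treated as whole-number totals; temporal stability r = 0.89; internal consistency 0.95; eligible baselines of 13 or more.

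**Inputs assumed, because the article gives none:** SD 6–9, screened mean 11–17, normally distributed scores.

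**1. The rule in points.** The smallest qualifying drop is 10% of baseline, rounded up.

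| Baseline | 10% of baseline | Drop needed |
|---|---|---|
| 13–20 | 1.3–2.0 | 2 |
| 21–30 | 2.1–3.0 | 3 |
| 31–36 | 3.1–3.6 | 4 |

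If the base is the scale, 0.10 × 36 = 3.6, so 4 points are needed throughout.

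**2. Retest error.** The SD of a retest difference is SD × √(2(1 − r)) = SD × √0.22 = 0.47 SD. The 95% bound is 1.96 × 0.47 SD = 0.92 SD:

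- SD 6: 5.5 points
- SD 7: 6.4 points
- SD 8: 7.4 points
- SD 9: 8.3 points

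The largest drop that the rule can require is 4 points. It falls below the bound once SD exceeds 4/0.92, about 4.4.

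**3. Rate with no true change, retest error alone** (differences centred on zero, continuity correction, SD 6–9, own-baseline reading): 30–36% at baselines 13–18, 19–28% at 22–28 and 11–20% at 36.

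**4. Rate with no true change, with selection.** I simulated two measurements with reliability 0.89, rounded them, clipped them to 0–36 and kept first scores of 13 or more (2 million draws per setting).

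- Mean 11–17, SD 6–9: 28–41% improve by 10% or more and 21–27% worsen by 10% or more.
- Mean 13, SD 7: about 36% improve and 24% worsen. Here 53% score 13 or more, in line with the Background's figure of about half with moderate-to-high FCR.
- 3.6-point reading: about 12–26% improve.
- 0.95 used as the reliability: 18–30% improve on the own-baseline reading.

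**5. Which SD a reliable-change bound would need.** Treated scores are cut off at 13, which shrinks their SD. At mean 13, SD 7:

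| SD used | SD | 1.96 × SD × √0.22 | Falsely improved |
|---|---|---|---|
| All treated | 4.3 | 4.0 | about 18% |
| Band 13–21 | 2.5 | 2.3 | about 26% |
| Band 22 or more | 2.9 | 2.7 | about 36% |

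Across the assumed grid, the false-improvement rate is about 7–20% with the SD of all treated participants and 18–50% with per-step SDs. With the nominal SD of everyone screened it is about 3–4%. It reaches about 6% in some settings if the SD is taken from the clipped scores.

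**The case against.** **The rate is not the protocol's.** A reader might infer that r = 0.89 by itself means about a third of unchanged participants would be called improved. The documents do not support that. The figure also needs an SD, a mean, a distribution and the own-baseline reading, and the article states none of these. A third lies within the assumed range but is not a derived value. This objection stands, and the rate should be given only as a range with its assumptions.

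**It is not all measurement error.** The excess of improvement over worsening in step 4 comes largely from selecting on the baseline score. The psychologist's discussion before allocation is a second filter that the simulation omits, and it could reduce that part. This also stands, although retest error alone (step 3) still gives rates well above zero.

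**Clinical importance and reliable change are different criteria.** A minimal important difference can lie below a 95% retest bound, and the source cited for 10% could not be checked. The standard error of one measurement is SD × √0.11 = 0.33 SD, or 2.0–2.7 points at SD 6–8, so the 3–4 points needed at 22 or more exceed one standard error. The review therefore cannot say that 10% is clinically wrong. What remains is that the rule cannot tell true change from retest change in an individual.

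**Change scores are already planned.** Descriptive statistics include means and medians, and change scores show worsening as well. This is so, but the article itself fixes a one-sided classification and its label, and those are what need changing.

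**Conclusion.** The point holds in a limited form. On the own-baseline reading the rule asks for 2–4 points, which is inside 95% retest error at r = 0.89 for any SD of about 4.4 or more. With no true change, a screened mean of 11–17 and an SD of 6–9, roughly 28–41% of those at 13 or more would be called improved and 21–27% would worsen by 10% or more. On the 3.6-point reading about 12–26% would be called improved. These rates combine retest error and regression to the mean, and the single arm can separate neither from an effect of the intervention.

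A reader might go further and conclude that the study's main objective is undermined. It is not. Acceptability and feasibility are the focus, Study aims calls the impact evaluation preliminary, and neither the feasibility criteria in Table 2 nor the sample size uses the responder rate. The consequence is a misleading label on one descriptive percentage. It should be fixed, but the study does not depend on it.

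**What to change.** Changes to the Impact section:

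- Make mean FCRI-SF change with a 95% CI, for each step, the main impact summary. State that without a control it still includes regression to the mean.
- Say what the 10% is a percentage of.
- Report the proportion with an increase of 10% or more beside the proportion with a reduction of 10% or more. The difference between the two is not an effect estimate, because selection at 13 or more favours reductions.
- Do not call the 10% rate a clinically significant improvement, and do not read it as evidence that the booklet improves FCR.
- If a reliable-change count is added, use 1.96 × SD × √(2(1 − 0.89)) with the SD of all screened participants, including those below 13, or an external SD. The SD of the treated group or of one step is truncated by selection and makes the bound too small.

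This changes wording and analysis only. It needs no new data beyond the screening and post-intervention scores already planned. The downside is a less favourable responder percentage.

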##### Exploratory analysis of FCR-1

Criterion validity [44] of the FCR-1 will be assessed using linear regression to examine associations between FCR-1 and FCRI-SF scores while controlling for known correlates of FCR, such as age and gender. Coefficients exceeding *r*=0.7 will be considered satisfactory [45].

A receiver operator characteristic (ROC) analysis will evaluate the ability of the FCR-1 to differentiate between clinical and non-clinical levels of FCR, as indicated by the classification criteria of a FCRI-SF score ≥22/36. An optimal cut-off score will also be determined.

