### Study aims

Our study aims to extend the *Fear-Less* stepped-care model to people with other types of cancer with early-stage disease. For our study, we have defined “early-stage disease” as survivors who have been treated with curative intent and who do not have metastatic disease. As per the *Fear-Less* model of care, individuals with moderate levels of FCR will be offered a clinician-guided self-management intervention and those with clinical levels of FCR will be offered ConquerFear.

The primary aim of our study is to evaluate the acceptability and feasibility of *Fear-Less* to treat FCR in survivors with early-stage disease. This will include evaluations from the perspectives of both survivors and clinicians. A preliminary evaluation of the impact of the stepped-care program on survivors’ FCR levels will also be conducted.

A second, exploratory aim is to assess a one-item measure of FCR, given a barrier to routine screening is the length of existing measures.

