##### Sample size

Sixty survivors will be recruited. As there is currently no clear consensus regarding appropriate sample size for feasibility studies [33], our target sample size is based on our previous feasibility study for *Fear-Less* amongst survivors with stage IV melanoma [32] and on available funding, resources (e.g., clinician time to deliver the stepped-care interventions), and study duration of 18 months. This sample size is also in line with previous pilot and feasibility trials [34].

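### The FCR-1 validity rule compares covariate-adjusted regression coefficients with r = 0.7, a benchmark on the correlation scale (minor, exploratory analysis)

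*Protocol article*

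**What the plan says.** The Protocol article presents this work as secondary. Under Study aims: "A second, exploratory aim is to assess a one-item measure of FCR". Under Exploratory analysis of FCR-1, criterion validity "will be assessed using linear regression to examine associations between FCR-1 and FCRI-SF scores while controlling for known correlates of FCR", with age and gender given as examples of those correlates. The pass rule follows directly: "Coefficients exceeding *r*=0.7 will be considered satisfactory".

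The section does not say which score is the outcome, or whether the coefficient is standardised, partial or unstandardised. Under FCR assessments, the two instruments have different ranges: for the FCRI-SF, "Total scores range from 0 to 36 with higher scores indicating higher FCR", while the FCR-1 is a single rating from 0 to 10. Under Sample size: "Sixty survivors will be recruited".

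The same section also plans a ROC analysis of FCR-1 against FCRI-SF of 22 or more, which is separate from the rule discussed here.

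**The concern.** Here criterion validity asks how closely the single item tracks the nine-item reference score. A threshold written as r = 0.7 answers that question when it is applied to the correlation between the two scores. The article fixes a different method, a regression that holds other variables constant, and puts the correlation threshold on its output. Method and threshold are both stated and they do not fit each other, so this is more than detail left to a fuller plan.

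At stake is the label given to the FCR-1. With a true correlation close to 0.7, the same data could be called satisfactory or not depending on the coefficient type, the outcome variable and the covariates entered. The covariate list is open ("known correlates of FCR, such as age and gender").

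**Working it through.** There is no sample size, power or alpha behind this rule to reproduce, so the check is algebra plus a simulation.

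**Inputs from the Protocol article:** benchmark 0.7; FCR-1 range 0 to 10; FCRI-SF range 0 to 36; n = 60.

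**Assumptions (the document gives no standard deviations or covariate correlations):** FCRI-SF SD 6 to 10; FCR-1 SD 2 to 3; covariate correlations between -0.4 and +0.1.

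**Notation:** x = FCR-1, y = FCRI-SF, z = one covariate such as age.

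**1. Standardised or partial coefficient (the natural reading).** With FCRI-SF as outcome:

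- standardised beta = (r_xy - r_xz·r_yz) / (1 - r_xz²)
- partial r = (r_xy - r_xz·r_yz) / √[(1 - r_xz²)(1 - r_yz²)]

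Downward: r_xy = 0.72 and r_xz = r_yz = -0.3 give (0.72 - 0.09) / (1 - 0.09) = 0.63 / 0.91 = 0.692 for both beta and partial r. The correlation passes and the adjusted value fails.

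Upward: r_xy = 0.68, r_xz = -0.3 and r_yz = -0.1 give beta = (0.68 - 0.03) / 0.91 = 0.714. The correlation fails and beta passes. Partial r here is 0.685 and still fails, so the coefficient type matters. With FCR-1 as the outcome, the same correlations give beta = 0.65 / 0.99 = 0.657, so the choice of outcome matters too.

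Partial r can also cross upward: r_xy = 0.68, r_xz = -0.2 and r_yz = +0.1 give 0.70 / √(0.96 × 0.99) = 0.718.

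Most of the shifts computed were about 0.02 to 0.05. One of the larger ones was 0.75 to 0.702, with both covariate correlations at -0.4. Some partial-r shifts were smaller, such as 0.68 to 0.685 above.

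**2. Chance of passing at n = 60** (10,000 simulated samples, true r = 0.72, both covariate correlations -0.3): 0.64 for the unadjusted correlation and 0.47 for the adjusted beta. Away from the threshold the two agree closely. At true r = 0.8 with covariate correlations of -0.25 the chances are 0.97 and 0.93, and at true r = 0.9 both are about 1.00.

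**3. Unstandardised slope.** Before adjustment:

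- FCRI-SF on FCR-1: b = r·SD_y / SD_x. It exceeds 0.7 once r > 0.7·SD_x / SD_y, which runs from 0.7 × 2/10 = 0.14 to 0.7 × 3/6 = 0.35. In simulation (SDs 8 and 2.5, true r = 0.5, covariate correlations -0.25) the adjusted slope passed in 98% of samples, against 0.8% for the correlation.
- FCR-1 on FCRI-SF: b = r·SD_x / SD_y. Even at r = 1 this is only 2/10 = 0.20 to 3/6 = 0.50, so 0.7 cannot be reached.

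**4. Precision of the plain correlation.** Fisher z for r = 0.70 and n = 60: 0.867 ± 1.96/√57 = 0.867 ± 0.260, which transforms back to 0.54 to 0.81.

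**The case against.** The strongest reply is that the symbol r already signals a correlation-scale coefficient. On that reading the shift is a few hundredths, while the 95% interval at n = 60 is 0.27 wide (0.81 - 0.54). Sampling error near the threshold therefore far exceeds the effect of adjustment, and the unadjusted correlation carries the same uncertainty. The covariate correlations are assumed, and because two of the three recruiting services are breast and gynecology, gender may vary little and adjusting for it may change little. All of this stands. It limits the size of the problem but does not remove it, since an adjusted coefficient is still not the quantity that 0.7 describes.

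Four stronger readings are tempting, and the document does not support them:

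- **That the rule is grossly wrong in practice.** The large errors in step 3 need someone to compare a raw slope with a value labelled r, which the wording discourages. They show only why the coefficient type should be named.
- **That this number decides whether one item can replace nine.** The article says only that the FCR-1 will be assessed and that a value above 0.7 is satisfactory. It also plans a separate ROC analysis. Allocation to care uses the FCRI-SF, and neither the feasibility criteria in Table 2 nor the impact analysis uses the FCR-1.
- **That the adjusted coefficient fails because it does not measure agreement.** Pearson and Spearman correlations do not measure agreement either, and the article claims only to examine associations.
- **That the ROC cut-off is also at fault.** The article says "An optimal cut-off score will also be determined" without naming a selection criterion. Internal validation and interval estimates are details that an article may leave to a fuller plan, and any figure for optimism would need an assumed criterion and prevalence. It is not part of this finding.

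**Conclusion.** The point holds as a minor correction. The article applies a correlation benchmark to a quantity that is not the FCR-1/FCRI-SF correlation. On the natural reading the discrepancy is roughly 0.02 to 0.05 in either direction, enough to change the verdict only when the correlation lies close to 0.7. That size rests on assumed covariate correlations. The mismatch between rule and method rests on the text alone. The analysis is exploratory, and allocation and the feasibility, acceptability and impact outcomes are unaffected.

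**What to change.** State that the 0.7 benchmark applies to the unadjusted Pearson (or Spearman) correlation between FCR-1 and FCRI-SF at screening, reported with its 95% confidence interval. Keep the age- and gender-adjusted regression as a supportive description with no threshold, and name its outcome variable, coefficient type and covariates. The cost is a change of analysis wording; no new data are needed.

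The change puts the rule on the right scale but does not make it precise. At n = 60 and a true correlation of 0.72, the unadjusted estimate still exceeds 0.7 in only about 64% of samples, so the interval should be read alongside the verdict.

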#### Qualitative data analysis

To assess acceptability, free text items from the survivor and clinician experience surveys will be analyzed using content analysis. A deductive approach will be used for coding data. Pre-defined categories will be formulated based on the research questions informing the study. Additional inductive codes will be identified from the survey responses.

